**Methods:**

100 participants will be enrolled: 60 from the Health Trust of Ferrara randomized 1:1:1 to (a) TAU, (b) rTMS + TAU, and (c) VR-COG + TAU, and 40 from the University Hospital of Cagliari randomized 1:1 to (a) TAU and (b) VR-COG + TAU. The inclusion criteria will be as follows: patients aged 18 years and older, both sexes, a diagnosis of oncological disease within the last 5 years in a non-advanced stage, a diagnosis of major depressive disorder according to DSM-5 criteria, and a score of≥14 on the 17-item Hamilton Rating Scale for Depression (HAM-D-17). The VR-COG program will include a series of exercises in virtual sailing scenarios using the software CEREBRUM. The rTMS program will be delivered at 50% of the resting motor threshold. Personalized targets created for each individual will be located at various cortical depths. TAU will include psychiatric visits and psychological counseling. All the interventions will last 3 months, with pre-post evaluation for outcomes of interest and 3-6 months of follow-up.

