**Conclusion:**

The monitoring of the program's cost-effectiveness, encompassing both the screening and intervention phases, will enable policymakers to inform the implementation of this evidence in routine clinical practice.

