### Outcomes

2.3

The following outcome measures will be established for each participant based on clinical relevance, Cochrane Collaboration indications, and cost-effectiveness studies.

The primary outcomes will include depressive symptoms and the study’s feasibility indicators (acceptability, tolerability, side effects, or secondary effects due to the use of technological devices).

The secondary outcomes will comprise quality of life, cognitive functions (immediate memory, working memory, phonemic verbal fluency, delayed memory, psychomotor speed, executive function, selective attention), and other depression-related conditions (demoralization, embitter-ment reactions to negative life events, psychological distress, insomnia, social and biological rhythms dysregulation, disability level, and alexithymia).

The tertiary outcome will include the cost-effectiveness of the nonpharmacological interventions (VR-COG, rTMS) in addition to TAU compared to TAU alone.

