
Toronto Alexithymia Scale 20-item (TAS-20) [43] is a self-report questionnaire designed to assess the degree of alexithymia. It consists of 20 items that measure three key dimensions of alexithymia: difficulty identifying feelings, difficulty describing feelings, and externally oriented thinking. The instrument demonstrates strong internal consistency, with Cronbach’s alpha ranging from 0.80 to 0.90. The questionnaire will be administered according to the following timeline: T0 (0 months-baseline), T1 (3 months-post-intervention), T2 (3 months after T1), and T3 (6 months after T1). A summary of the timeline is provided in Fig. (**1**).

The tertiary outcome will be measured as cost-effectiveness [3] of the nonpharmacological treatments (VR-COG and rTMS), and it will be computed as the ratio of total costs divided by the mean improvements of quality of life across interventions (TAU, TAU+rTMS, TAU+VRCOG). Total costs will include the costs of the healthcare consultations (visits in the TAU condition), psychotropic drugs, equipment, and staff. Total costs will be computed as the sum of the costs of each intervention, divided by the number of patients. Quality of life improvements will be computed as the difference between the baseline (T0) and the endpoint (T3) quality of life. A summary of the timeline is provided in Fig. (**1**).

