### Statistical Analysis

2.11

The baseline data will be summarised as percentage (absolute numbers) for qualitative variables and median (1^st^ and 3^rd^ quartiles) for continuous variables. The group sequential Bayesian design [49] will be used to analyze the study's primary endpoints. Additionally, the first interim analysis will be carried out when 70% of enrolment is reached. The pattern chosen for the evaluation of the risk ratios of the primary endpoint will be defined by a beta-binomial model [50]. Apart from that, a SHELF (Sheffield Elicitation Framework) elicitation paradigm [51] will be used to define the prior probability of remission in the three intervention groups. The elicitation procedure will be carried out using R Shelf software [52]. Non-informative priors will still be used for sensitivity analyses. Upon reaching the interim, the probability that the posterior RR (relative risk) estimates, for the TAU *versus* rTMS or TAU *versus* VR-COG comparison, imply a value greater than 1 and surpass an efficacy boundary established in the interim, will be calculated. If at least one posterior probability for comparison using informative and non-informative priors exceeds the interim boundaries, then the trial will end due to efficacy; otherwise, the trial will continue until the end of the study. If the trial advances, the posterior probabilities for the RRs, with 95% confidence intervals, will be calculated. The intervention will be considered effective if the posterior probability that the RR exceeds 1 is higher than the ultimate effectiveness boundary. Secondary analyses will be performed using generalized Bayesian models by taking into account the interventions as a covariate and reporting 95% posterior confidence intervals. The convergence of the models will be evaluated using trace plots and Gelman statistics. The data will be analysed with an intention-to-treat approach and imputation of missing data according to a Last Observation Carried Forward (LOCF) protocol [53].

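### The per-arm ratio of cost to quality-of-life change does not estimate cost-effectiveness against TAU, and it breaks down when an arm's mean change is near or below zero

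*Protocol article*

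**What the plan says.** The tertiary outcome is defined in section 2.4 (Evaluation Tools and Evaluation Timeline): "it will be computed as the ratio of total costs divided by the mean improvements of quality of life across interventions", with the three arms then listed in brackets.

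- Numerator: "Total costs will be computed as the sum of the costs of each intervention, divided by the number of patients".
- Denominator: "Quality of life improvements will be computed as the difference between the baseline (T0) and the endpoint (T3) quality of life". It is a change within the arm, not a difference from TAU. The section does not say which quality-of-life measure is meant; EQ-5D (descriptive part and VAS) and SF-12 are both collected at T0 to T3.
- Question: section 2.3 (Outcomes) defines the tertiary outcome as "cost-effectiveness of the nonpharmacological interventions (VR-COG, rTMS) in addition to TAU compared to TAU alone".
- Use: the abstract's Conclusion says that monitoring cost-effectiveness "will enable policymakers to inform the implementation of this evidence in routine clinical practice".
- Intervals: section 2.11 says "Secondary analyses will be performed using generalized Bayesian models by taking into account the interventions as a covariate and reporting 95% posterior confidence intervals". This is not tied to the tertiary outcome.

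**The concern.** The formula is written out, so an analysis plan that follows it inherits its properties. Two of these are unwelcome.

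First, each arm is credited with its whole before-after change, including whatever change would have occurred under TAU. The extra cost and extra benefit of adding rTMS or VR-COG never appear in the calculation.

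Second, cost is always positive, but mean quality-of-life change can take either sign. A ratio with such a denominator has no meaning at zero, turns negative below it, and swings widely on either side.

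Cost-effectiveness is in the title and underlies the statement about policymakers. The misleading result would therefore fall on the economic message of the trial, although the outcome is only tertiary.

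**Working it through.** The article gives no cost, quality-of-life change, SD or cost-effectiveness figure, so there is no stated result to reproduce. All costs, effects, SDs and values of d below are assumptions.

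**Arm sizes.** The abstract's Methods give, for the first unit, "60 from the Health Trust of Ferrara randomized 1:1:1 to (a) TAU, (b) rTMS + TAU, and (c) VR-COG + TAU". Ferrara therefore has 60/3 = 20 per arm. The second unit, Cagliari, splits its 40 patients equally over two arms, TAU alone and VR-COG with TAU: 40/2 = 20 per arm. Totals: TAU 40, VR-COG 40, rTMS 20. At 70% this is 28, 28 and 14, which matches the Sample Size section.

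**Behaviour at and below zero.** Ratio = mean cost / mean change.
- At zero change it is undefined.
- Two arms each worsening by 0.05, with costs 2,000 and 3,000: 2,000/(-0.05) = -40,000 and 3,000/(-0.05) = -60,000. The costlier arm has the lower value, and both lie below any improving arm.
- Same cost of 2,000, worsening by 0.01 or 0.10: -200,000 and -20,000. The larger worsening gives the less extreme value.

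**How likely is a non-positive mean change?** With d = true mean change / SD of change, P(arm mean ≤ 0) = Φ(-d√n). The arms are independent, so P(at least one) = 1 - Π[1 - Φ(-d√n)].

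| d | TAU or VR-COG (n = 40) | rTMS (n = 20) | At least one of three |
|---|---|---|---|
| 0 | 50% | 50% | 87.5% |
| 0.1 | 26.4% | 32.7% | 63.5% |
| 0.2 | 10.3% | 18.6% | 34.5% |
| 0.3 | 2.9% | 9.0% | 14.2% |
| 0.5 | 0.1% | 1.3% | 1.4% |
| 0.8 | about 0 | about 0 | about 0 |

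For scale, a utility gain of 0.05 with SD 0.25 is d = 0.2.

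One simulated scenario took SD 0.2, true changes of 0.02 (TAU), 0.06 (rTMS) and 0.06 (VR-COG), and costs of 600, 3,000 and 2,000. The lowest ratio belonged to a worsening arm in 35% of trials. The formula agrees: 1 - 0.736 × 0.910 × 0.971 = 0.35.

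**Per-arm against incremental.** All three arms improve here, so no sign problem arises.

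| Arm | Mean cost | Mean change | Per-arm ratio | Incremental ratio against TAU |
|---|---|---|---|---|
| TAU | 600 | 0.05 | 12,000 | – |
| VR-COG + TAU | 2,000 | 0.10 | 20,000 | 1,400/0.05 = 28,000 |
| rTMS + TAU | 3,100 | 0.15 | 20,667 | 2,500/0.10 = 25,000 |

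The per-arm ratio puts TAU first and VR-COG ahead of rTMS. The incremental ratio puts rTMS ahead of VR-COG. At an assumed willingness to pay of 30,000 per unit of effect, net benefit against TAU is 30,000 × 0.05 - 1,400 = 100 for VR-COG and 30,000 × 0.10 - 2,500 = 500 for rTMS. Both add-ons would then be preferred to TAU, the reverse of the per-arm order.

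**Can an interval be attached?** Yes. A bootstrap of 40 invented patient records (cost and change for each patient) gave a ratio of 16,098, 95% interval 10,289 to 32,645. Whether an interval helps depends on the denominator. With cost fixed at 2,000, n = 40 and SD 0.2, the central 95% of simulated ratios was:
- d = 0.5 (true ratio 2,000/0.10 = 20,000): about 12,300 to 52,100;
- d = 0.2 (true ratio 2,000/0.04 = 50,000): about -417,000 to 493,000, which cannot be interpreted.

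**The case against.** **The true changes may not be small.** Patients enter with a HAM-D-17 score of at least 14, and the Sample Size section assumes 60% remission on TAU and an SMD of 0.90 for VR-COG. If quality of life moved in proportion, d would exceed 0.5 and a non-positive mean would be rare. This stands as a limit on the sign problem. It does not settle the matter: those are depression figures, the endpoint T3 is six months after treatment ends, and Study Limitations itself expects clinical instability and fluctuating symptoms.

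**Uncertainty methods may sit in the analysis plan.** This stands too. A reader might infer from the wording that the ratio can carry no uncertainty, or that no patient-level cost will exist. The article supports neither. Quality of life is measured per patient, a total divided by the number of patients is simply a mean, and nothing rules out costs recorded per patient. The absence of a stated interval is not the point here.

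**No ranking rule is written.** Correct. Treating a negative ratio as the best value would be the analyst's mistake, and the article does not prescribe it. But a separate ratio for each of three arms invites comparison between them, and section 2.3 asks for one.

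**The outcome is tertiary in a self-described pilot.** This lowers the weight. The pilot caveat concerns clinical efficacy, however, and does not qualify the policy statement.

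**Conclusion.** The point holds as a defect in a stated method. The per-arm ratio does not estimate the comparison in section 2.3, and arms compared by it can fall in the wrong order even when all improve. That part needs no assumption about d; the numerical example only illustrates it.

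The ratio is also undefined, negative or uninterpretable when an arm's mean change is at, below or near zero. The size of this depends on an unknown: about 64%, 35%, 14% and 1.4% for at least one non-positive arm at d = 0.1, 0.2, 0.3 and 0.5. A reader might conclude that 20 rTMS patients can never fix the sign of the change. That is true only for small d: for rTMS alone the chance is 33% at d = 0.1 and 1.3% at d = 0.5.

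The method should be changed. The matter does not touch the primary analysis.

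**What to change.** In section 2.4, replace the per-arm ratio with incremental cost (ΔC) and incremental effect (ΔE) for each add-on arm against TAU, computed from patient-level costs. Name the effect measure, for example the EQ-5D utility, and state that change is T3 minus T0 so that improvement is positive.

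Summarise the result as net monetary benefit, λΔE - ΔC, over a stated range of willingness to pay λ, with a bootstrap or posterior interval. An incremental ratio alone would bring back the denominator problem when ΔE is near zero; net benefit is linear and defined for any ΔE. Do not compare arms by the average ratio.

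Cost: a change of wording, assignment of visits, drugs, staff and equipment to individual patients, and some extra analysis. EQ-5D is already collected at T0 to T3, so no visit, instrument or patient is added. The downside is that the result will look less certain.

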### Study Design

2.1

The study will involve a randomized controlled trial (RCT) among persons with oncological diseases and mild-moderate depression. The study will include a longi-tudinal, three-arm design with participants assigned by randomization to either an active interventional protocol based on repetitive transcranial magnetic stimulation (rTMS) + treatment as usual (TAU) or virtual reality-based cognitive remediation (VR-COG) + TAU, and to a control setting, treatment as usual (TAU). The main outcomes are expected to show the superiority of each experimental intervention (rTMS + TAU or VR-COG +TAU) over the control condition (TAU). Participants will be randomized, independently, to parallel intervention groups in each of the two units [unit 1, Health Trust of Ferrara (UniFE), with 1:1:1 randomization to (a) TAU, (b) rTMS + TAU, and (c) VR-COG + TAU; unit 2, University Hospital of Cagliari (UniCA), with 1:1 randomization to (a) TAU and (b) VR-COG + TAU] with the stratification for the unit of the recruitment.

The timeline of the different study phases and the protocol flow diagram are presented in Figs. (**1** and **2**), respectively.

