#### Control: Treatment as Usual (TAU)

2.9.1

Treatment as usual (TAU) path, following the guidelines of the Italian Association of Medical Oncology (AIOM-SIPO: https://www.aiom.it), is an active comparator and includes an initial psychiatric visit aimed at assessing the presence of psychopathological conditions that may necessitate pharmacological therapy and subsequent psychiatric follow-up. The treatment will also involve psychological counselling (bi-monthly sessions) for 12 consecutive weeks. The duration of each session will be 50 minutes.

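### The cost-effectiveness rule gives each arm's own average cost per unit of quality-of-life change, which does not answer the stated question of adding a device to TAU

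*Protocol article*

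**What the plan says.** Section 2.3 (Outcomes) sets the tertiary outcome as the "cost-effectiveness of the nonpharmacological interventions (VR-COG, rTMS) in addition to TAU compared to TAU alone".

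Section 2.4 (Evaluation Tools and Evaluation Timeline) then fixes the computation:

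- The measure: "it will be computed as the ratio of total costs divided by the mean improvements of quality of life across interventions". The three arms (TAU, TAU+rTMS, TAU+VRCOG) are listed directly after.
- The numerator: "Total costs will be computed as the sum of the costs of each intervention, divided by the number of patients". Its components: "Total costs will include the costs of the healthcare consultations (visits in the TAU condition), psychotropic drugs, equipment, and staff".
- The denominator: "Quality of life improvements will be computed as the difference between the baseline (T0) and the endpoint (T3) quality of life".

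Section 2.9.1 says that TAU "is an active comparator and includes an initial psychiatric visit", and both experimental arms receive TAU as well. Section 2.11 (Statistical Analysis) does not mention cost-effectiveness. Nowhere does the article mention an incremental cost, incremental effect, incremental ratio or net benefit.

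**The concern.** The question in section 2.3 is incremental: what does the device add to TAU, and at what extra cost? The rule in section 2.4 contains no contrast with TAU in either term. A device arm's change from baseline includes the effect of TAU, natural recovery and regression to the mean. All of these also occur in the TAU arm, and only a between-arm difference removes them. The device arm's cost likewise includes the cost of TAU.

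Cost-effectiveness is in the article's title, and the abstract, discussion and conclusion offer it to policymakers. If the rule is followed, they receive a figure that is not the price of the added benefit.

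This is not a detail left to an analysis plan. The article states numerator, denominator and time points, so a later plan must either inherit the rule or contradict it.

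**Working it through.** The article prints no cost-effectiveness result, so there is no figure to reproduce. The check compares two formulas.

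**Notation.** C0 and E0 are mean cost and mean T0-to-T3 quality-of-life gain under TAU. C1 = C0 + dC and E1 = E0 + dE are the same for an add-on arm.

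- Planned ratio (section 2.4): C1/E1 = (C0 + dC)/(E0 + dE)
- Incremental ratio (what section 2.3 asks for): dC/dE

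**1. Relation between the two.** If E0 > 0 and dE > 0, the planned ratio lies between C0/E0 and dC/dE. It equals the incremental ratio only when dC/dE = C0/E0. It understates the price of the added benefit if the device costs more per unit than TAU, and overstates it if the device costs less. If dE is negative, this ordering no longer holds.

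**2. Size under the plan's own remission rates.** Section 2.11.1 assumes remission of 0.6 under TAU and a risk ratio of 1.5, hence 0.6 × 1.5 = 0.9. Assume, without support in the article, that quality-of-life gain is proportional to remission, so E1 = 1.5 E0. Let the device add k times TAU's cost, so dC = k C0.

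- Planned: (1 + k)C0/(1.5 E0)
- Incremental: k C0/(0.5 E0)
- Incremental ÷ planned = 3k/(1 + k)

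| k | incremental ÷ planned |
|---|---|
| 0.25 | 0.75/1.25 = 0.6 |
| 0.5 | 1.5/1.5 = 1.0 |
| 1 | 3/2 = 1.5 |
| 4 | 12/5 = 2.4 |

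Below k = 0.5 the planned ratio overstates the price; above it, it understates it. The limit for large k is 3.

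**3. Behaviour over assumed inputs.** All of these are assumptions: C0 = 1,000; C1 = 2,000 to 4,000; E0 = 0.05 to 0.15; dE from -0.02 to 0.10.

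- dE = 0 (no added benefit): the planned ratio runs from 2,000/0.15 = 13,333 to 4,000/0.05 = 80,000. The incremental ratio is undefined.
- dE = -0.02 (dearer and worse): the planned ratio runs from 2,000/0.13 = 15,385 to 4,000/0.03 = 133,333, still positive.
- dE = 0.02: the incremental ratio is 50,000 to 150,000, against planned ratios of 11,765 to 57,143. It is 1.75 to 6.4 times larger.
- C1 = 2,000, E0 = 0.05, dE = 0.10: planned 2,000/0.15 = 13,333; incremental 1,000/0.10 = 10,000; TAU's own ratio 1,000/0.05 = 20,000. Here the planned ratio overstates the price, and the dearer arm ranks ahead of TAU.

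**4. Stability of the denominators.** Assume a standard deviation of 0.15 to 0.25 for the change score.

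- Planned ratio, true arm gain 0.05: P(mean ≤ 0) = Φ(-0.05√n/SD), which is 7 to 19% with 20 patients and 2 to 10% with 40.
- Incremental ratio, true extra gain 0.025: P(difference ≤ 0) = Φ(-0.025/(SD√(1/n1 + 1/n0))). With 40 v 40, z = 0.745 to 0.447, giving 23 to 33%. With 20 v 20, z = 0.527 to 0.316, giving 30 to 38%.

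Under these assumptions the incremental ratio is the less stable of the two, which bears on the remedy.

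**The case against.** The strongest reply is that all three arms, TAU included, are listed under the measure, so the arm figures can be set side by side. That is true. If mean cost and mean change are reported by arm, a crude incremental ratio follows by subtraction. It would therefore go too far to say that the randomised comparison is lost or that the planned data cannot answer the question; the fault is in the chosen summary. But comparing or subtracting average ratios, which is the most that the phrase about interventions could mean, still does not give extra cost per extra benefit.

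A reader might also infer that the rule always flatters the devices, because it credits them with TAU's improvement. The article does not support this: TAU visits are in total costs, so the device arms carry TAU's cost too, and the error can run either way. Nor does ranking on the ratio always favour the cheapest arm. It favours TAU when cost rises proportionally more than gain, and the add-on when it does not. What stands is that the ranking takes no account of what the extra gain is worth.

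An incremental ratio is itself unstable when the extra gain is near zero. This stands, and it is why net benefit should lead. Finally, the outcome is tertiary, and section 4 describes the study as a pilot giving exploratory evidence. That lowers the urgency, but it does not make the rule answer the stated question.

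**Conclusion.** The concern holds: the rule in section 2.4 is wrong as written for the question in section 2.3. It yields an average cost per unit of uncontrolled change in each arm, not the cost of an additional unit of benefit over TAU.

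The direction and size of the error cannot be known from the article. The factors 0.6, 1.5 and 2.4 rest on gain being proportional to remission, and the other figures rest on invented costs and gains. That a useless or harmful device can still show an unremarkable positive ratio needs only a positive overall gain in its arm.

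The primary outcomes, power and safety assessments are untouched. For a tertiary outcome in a pilot, this should be fixed rather than treated as blocking, although its place in the title and the promise to policymakers argue for more weight.

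**What to change.** Replace the rule in section 2.4 with the following.

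- For each add-on arm versus TAU, estimate the between-arm difference in mean cost, with TAU care costed in all three arms, and the between-arm difference in quality of life adjusted for its baseline. Name the quality-of-life measure used. EQ-5D and SF-12 are both planned at T0 to T3, and the EQ-5D description leaves the three- or five-level version open.
- Compare rTMS + TAU only with TAU patients randomised concurrently at the same unit. Sections 2.1 and the abstract place rTMS in Ferrara, but the worked example in section 2.11.1 names Cagliari; these must be reconciled. Stratify the VR-COG comparison by site.
- Report incremental net benefit with its uncertainty as the main summary. Give the incremental ratio alongside, with the caveat that it is unstable when the extra gain is near zero.
- Draw no conclusion from arm-level average ratios.

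The cost is revised wording and a little extra analysis on data already planned for collection. Intervals will be wide at this sample size, with 20 patients per arm in the rTMS comparison, and the report should say so.

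### The cost-effectiveness formula gives each arm its own average ratio, so it does not measure what adding rTMS or VR-COG to TAU costs per extra unit of quality of life

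*Protocol article*

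**What the plan says.** Section 2.3 (Outcomes) defines the tertiary outcome as the "cost-effectiveness of the nonpharmacological interventions (VR-COG, rTMS) in addition to TAU compared to TAU alone".

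The last paragraph of Section 2.4 (Evaluation Tools and Evaluation Timeline) gives the calculation. Cost-effectiveness is "computed as the ratio of total costs divided by the mean improvements of quality of life across interventions", with TAU, TAU+rTMS and TAU+VR-COG listed as the three interventions. For the numerator, "Total costs will be computed as the sum of the costs of each intervention, divided by the number of patients". For the denominator, "Quality of life improvements will be computed as the difference between the baseline (T0) and the endpoint (T3) quality of life". The cost categories are consultations, psychotropic drugs, equipment and staff.

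No section defines a cost difference, an effect difference, an incremental ratio or a net benefit. The Statistical Analysis section (2.11) does not mention the cost-effectiveness analysis. The Abstract, Section 3 and the final Conclusion say that the result is meant to guide policymakers.

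**The concern.** The question is comparative: what does the add-on cost beyond TAU, and what does it gain beyond TAU? The formula has no comparison in it. TAU receives a ratio of its own and does not serve as the reference to be subtracted.

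A within-arm change from T0 to T3 mixes the effect of the add-on with everything else that moves quality of life over those nine months, including TAU itself and natural recovery. Randomization is there to remove that component, and this formula puts it back. The resulting figure is not the extra cost per extra unit of quality of life, which is what a policymaker deciding on the add-on needs. Cost-effectiveness is also the first word of the article's title.

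This is not a detail left to an analysis plan. The article fixes the ratio, its numerator, its denominator and its time points, and an analysis plan that followed it would carry the wrong quantity forward.

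**Working it through.** The article reports no cost, quality-of-life gain or threshold, so there is no figure of its own to reproduce. The check compares two formulas under assumed inputs.

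**Formulas.** C is mean cost per patient and E is mean T0-T3 change.
- As written, for each arm: C / E.
- As the question in Section 2.3 requires: (C_add-on − C_TAU) / (E_add-on − E_TAU).

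**Assumed inputs** (cost units; none is from the article): C_TAU = 600, C_add-on = 2,400, extra gain = 0.05. The incremental ratio is (2,400 − 600) / 0.05 = 1,800 / 0.05 = 36,000 throughout. Only the TAU arm's own gain varies.

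| TAU gain | TAU ratio as written | Add-on ratio as written | Incremental ratio |
|---|---|---|---|
| 0.01 | 600/0.01 = 60,000 | 2,400/0.06 = 40,000 | 36,000 |
| 0.02 | 600/0.02 = 30,000 | 2,400/0.07 = 34,286 | 36,000 |
| 0.05 | 600/0.05 = 12,000 | 2,400/0.10 = 24,000 | 36,000 |
| 0.10 | 600/0.10 = 6,000 | 2,400/0.15 = 16,000 | 36,000 |
| 0.15 | 600/0.15 = 4,000 | 2,400/0.20 = 12,000 | 36,000 |

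The add-on's value relative to TAU is identical in every row, yet its ratio as written runs from 40,000 down to 12,000. It looks better than TAU in the first row and worse in all the others.

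**Where the ranking flips.** Setting 600/e = 2,400/(e + 0.05) gives 1,800e = 30, so e = 0.0167. At that point both ratios equal 36,000. When both gains and the extra gain are positive, the add-on looks better than TAU exactly when the incremental ratio is below TAU's own average ratio. The formula therefore sets a hidden threshold from TAU's before-after change.

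**Two boundary cases with the same costs.**
- Both arms gain 0.05. The add-on ratio is 2,400/0.05 = 48,000 and the TAU ratio is 12,000. The ranking is right, but a finite 48,000 hides that the add-on costs 1,800 more for no extra gain.
- TAU changes by −0.02 and the add-on by +0.03. The TAU ratio is 600/(−0.02) = −30,000, which has no useful meaning, and the add-on ratio is 2,400/0.03 = 80,000. The increment is still 0.05, so the incremental ratio is still 36,000.

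**Wording.** The phrase about interventions could be read as one pooled ratio over all arms. A pooled ratio is not incremental either, so the conclusion does not depend on the reading.

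**The case against.** The best case for the plan is that this is a tertiary outcome in a study whose limitations section (Section 4) calls it a pilot that gives exploratory evidence. The formula touches no primary endpoint, efficacy boundary or sample size. The arm means it requires are also the components of an incremental ratio, so nothing is lost if the formula is corrected before analysis. All of this stands, and it lowers the priority of the point. It does not make the written formula answer the question in Section 2.3.

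Four stronger readings are tempting, and the article does not support them.

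- **That an incremental ratio cures undefined or negative values.** It does not. It has the same trouble when the incremental effect is near zero or negative, which is an argument for net benefit.
- **That using only T0 and T3 is an error.** Sustained change at the last visit is a legitimate effect measure. The article speaks of quality of life, not QALYs, and the T1 and T2 values are still collected for the secondary outcome. An area under the curve would count a benefit that fades by T3, but that is a choice of method.
- **That a missing screening cost distorts the comparison.** The Abstract says the monitoring is one "encompassing both the screening and intervention phases", and the cost list in Section 2.4 does not name screening. Yet screening precedes randomization, so its cost is equal in expectation across arms and cancels from the incremental cost. The staff or consultation categories might also include it.
- **That the lack of acceptability curves or a willingness-to-pay value is a defect.** These normally belong in a full protocol or health-economic plan, which is not shown.

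**Conclusion.** The point holds. Section 2.4 fixes an average ratio for a question that Section 2.3 frames as incremental. Under the assumed inputs, one fixed incremental ratio of 36,000 goes with add-on ratios from 12,000 to 40,000, and the ranking against TAU reverses at a TAU gain of about 0.017. Those numbers rest wholly on assumed costs and gains. The structural fault does not: a ratio that never subtracts TAU cannot isolate the extra cost per extra unit gained.

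A reader might infer that the trial's cost-effectiveness result will be wrong. The article does not show that. It shows that the stated formula can mislead, depending on how the TAU arm fares. The priority is should-fix: the outcome is tertiary, but cost-effectiveness is in the title and is offered to policymakers.

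**What to change.** Replace the formula in Section 2.4 with two quantities for each add-on versus TAU: the difference in mean cost per patient and the difference in mean quality-of-life change.

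- **VR-COG+TAU versus TAU:** both sites, with site accounted for.
- **rTMS+TAU versus TAU:** concurrent TAU patients at the site that randomizes to rTMS. The Abstract and Section 2.1 give this as Ferrara. The example in Section 2.11.1 names Cagliari, and the two must be reconciled.
- **Reporting:** an incremental ratio or, preferably, incremental net benefit (value per unit × effect difference − cost difference) with its uncertainty, because net benefit stays defined when the effect difference is near zero or negative.

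Optional additions:
- Use the EQ-5D values already collected at T0, T1, T2 and T3 as an area under the curve, adjusted for baseline.
- Align the statement that the evaluation covers screening with the cost list, noting that screening cost cancels from the incremental comparison.

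The cost is new wording, a little more analysis, and choosing one quality-of-life measure, since both EQ-5D and SF-12 are collected. If EQ-5D is chosen, its version must be settled, because Section 2.4 mentions both the three-level and the five-level form. No new data collection is needed.
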